## 1. Purpose and significance

Exercise training is one of the most effective strategies for decreasing the likelihood of age- and lifestyle-related diseases, thereby promoting independence and enhancing the quality of life in the rapidly growing elderly populations of many countries (1, 2). Recent guidelines suggest that to achieve the desired effects, an exercise program should be tailored to an individual's fitness level, and in most cases, individualized training is performed using exercise equipment, stationary bicycles, and treadmills at a gymnasium or related facility where the exercise intensity can be more easily monitored. However, these training programs are costly and limit adherence to training programs (3).

To solve these problems, we recently developed a broadly available, remotely supervised exercise training system for middle-aged and older individuals. The system consists of interval walking training (IWT) and an IT network for monitoring exercise intensity and volume during IWT for a large population of middle-aged and older people. The IWT is a training regimen repeating  $\geq 5$  sets of fast walking at  $\geq 70\%$  individual peak aerobic capacity ( $VO_{2peak}$ ) and slow walking at  $\sim 40\%$   $VO_{2peak}$  for 3 minutes each and  $\geq 4$  days/week, during which exercise intensity (energy expenditure per min) was measured with a portable calorimeter equipped with a tri-axial accelerometer and barometer. The purpose of this study is to assess the preventive and therapeutic effects of increased physical fitness by interval walking training on age-associated diseases in middle-aged and older people.

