### 3.1. Inclusion criteria

- 1) Persons, aged 40 to 85 years, participating in a health promotion program for middle-aged and elderly citizens, the "Active Health Square by The Matsumoto Physical Training Program for Senior Citizens" project.
- 2) Those who can walk independently.

- 3) Those who have received their home doctors' permission to participate in the study.
- 4) Those who gave us their informed consents after explained about the details of the study.

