## 4. Study methods

### 4.1. Study design

- Single arm intervention

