### 4.2. Study outline

The protocol of this study is shown below. Physical characteristics, blood pressure, blood lipids and glucose, peak aerobic capacity ( $VO_{2peak}$ ), thigh muscle strength, CES-D, bone mineral density, and markers for calcium metabolism are measured before and after the IWT regimen.

IWT regimen: Before the start of training, subjects are invited to a community office near their homes and instructed to repeat >5 sets of 3-minute low-intensity walking at ~40% of the pretraining  $VO_{2peak}$  for walking followed by 3-minute high intensity at  $\geq 70\%VO_{2peak}$  for  $\geq 4$  days/wk. The energy expenditure during daily walking at their favorite time and place is monitored with a triaxial accelerometer (Jukudai Mate; Kissei Comtec, Matsumoto, Japan) on the right or left waist on the midclavicular line. A beeping signal alerts participants when a change of intensity is scheduled.

Every 2 weeks, the participants visit a local office to transfer their walking records from the accelerometer to a central server at the administrative center through the Internet for automatic analysis and reporting. Trainers use these reports to track daily walking intensity and other parameters to instruct participants on how best to achieve the target

levels.

[figure not shown]

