## 5.2. Assignment methods and assignment-regulating factors

This is not applicable because this study is single-arm intervention.

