## 6. Outcomes

Primary outcomes: Peak aerobic capacity before and after interval walking training

Secondary outcomes: Age-associated disease symptoms; the symptoms of lifestyle-related diseases (hypertension, hyperglycemia, obesity and dyslipidemia), orthopedic diseases (chronic osteoarthritis and osteoporosis), and psychiatric disorders (insomnia, depression, and dementia)

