#### 10.3.3. Analysis regarding accessory endpoints

We expect that after the intervention, increases in physical fitness will be accompanied by improvements in age-associated diseases.

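### Section 1 aims at preventive and therapeutic effects on disease, which a single-arm before/after study with no new-onset outcome cannot show

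*Protocol*

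**What the plan says.** Protocol Section 1 gives the purpose: to "assess the preventive and therapeutic effects of increased physical fitness by interval walking training on age-associated diseases in middle-aged and older people".

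The design sections then fix what can be learned:

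- Section 4.1 gives the design as "Single arm intervention". Section 5.2 says of assignment: "This is not applicable because this study is single-arm intervention".
- Section 4.2 lists fitness, blood pressure, lipids, glucose, CES-D, bone density and calcium markers, which "are measured before and after the IWT regimen". The schedule in Section 7 has one pre-training and one post-training assessment for these items.
- Section 3.1 admits "Persons, aged 40 to 85 years, participating in a health promotion program for middle-aged and elderly citizens" and "Those who can walk independently", with a home doctor's permission and consent. Neither 3.1 nor 3.2 requires or excludes any of the diseases of interest.
- Section 6 makes peak aerobic capacity primary. Disease enters as secondary symptoms: lifestyle-related diseases, "orthopedic diseases (chronic osteoarthritis and osteoporosis), and psychiatric disorders (insomnia, depression, and dementia"). No item is the onset of a new condition.
- Section 10.2 plans repeated-measures ANOVA for change after training, and ANCOVA or multiple regression for covariates that it does not name.
- Section 10.3.2 is headed as hypothesis verification, while Sections 10.1 and 13 call the study exploratory. Section 10.3.3 expects that "increases in physical fitness will be accompanied by improvements in age-associated diseases".
- Section 18.1 closes registration on 30 September 2009 and ends the study on 31 March 2010.

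**The concern.** The purpose joins two causal aims. Prevention concerns people free of a condition and asks whether fewer of them develop it than would have done untrained. Therapy concerns people who have the condition and asks whether they improve more than they would have untrained. Both need an estimate of what happens without training, and prevention also needs new onset to be an outcome over a period long enough to see it. The protocol provides none of these. After Section 1 prevention is not taken up again: Sections 10.3.2 and 10.3.3 speak only of improvement.

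At stake is what the study may conclude. A report that followed Section 1 literally would present a before/after difference as evidence of preventing or treating disease, whatever the data showed. The measurement of fitness itself is not in question here.

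**Working it through.** **No plan figure to reproduce.** The target of 1000 (Section 9) has no effect size, SD, event rate or dropout behind it, and Section 10.1 says the number needed for 80% power is unclear. The point rests on the design, and the figures below only show scale.

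**1. What one arm identifies.**

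- Therapy: observed mean change = training effect + change that would have occurred anyway. One arm estimates only the sum.
- Prevention: effect = untrained incidence − trained incidence. The first term is never observed, and the second is not an outcome in Section 6.

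**2. Length of follow-up (Section 18.1).** From 30 September 2009 to 31 March 2010: 31 + 30 + 31 + 31 + 28 + 31 = 182 days, about 6 months at most for the last registrant. The last dated column in Section 7 is 5 months after the start. The post-training assessment is a separate, undated column, and no later assessment is scheduled for anyone.

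**3. Sensitivity to drift.** Inputs: n = 1000 (Section 9), two-sided 0.05 (Section 10.3), 80% power (Section 10.1). Detectable mean change, in SDs of the change = (1.960 + 0.842)/√n:

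- n = 1000: 2.802/31.62 = 0.089
- n = 800: 0.099
- n = 500: 0.125

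Shifts of this size from season, drug changes or repeat testing would often be significant, with no control to remove them.

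**4. New cases (assumed inputs).** Annual incidence i = 1-5%; 500-900 of the 1000 free of the condition. Expected cases = n_free × [1 − (1 − i)^t], t in years:

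- t = 5/12, low end: 500 × (1 − 0.99^(5/12)) = 2.1
- t = 5/12, high end: 900 × (1 − 0.95^(5/12)) = 19.0
- t = 1/2: 500 × 0.00501 = 2.5 to 900 × 0.02532 = 22.8

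So the choice between 5 and 6 months hardly matters. For scale, take a hypothetical 1:1 controlled comparison aiming at an assumed 30% risk reduction over 5 months (two-sided 0.05, 80% power). With p₁ = 1 − (1 − i)^(5/12), p₂ = 0.7p₁ and p̄ their mean,

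n per arm = [1.960√(2p̄(1−p̄)) + 0.842√(p₁(1−p₁) + p₂(1−p₂))]² / (p₁ − p₂)².

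- i = 5%: p₁ = 0.0211, about 6,900 per arm
- i = 1%: p₁ = 0.0042, about 35,400 per arm

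**5. Would splitting by a baseline reading rescue the therapeutic claim? (assumed inputs)** Take a normal marker, zero training effect, prevalence p = 10-50% above a cut-off c, and test-retest correlation r = 0.6-0.9. Fall in the affected group = (1 − r) × φ(c)/p, in SDs of the marker; rise in the unaffected group = that fall × p/(1 − p).

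- Largest fall (p = 0.1, r = 0.6): 0.4 × 0.1755/0.1 = 0.70 SD
- Smallest fall (p = 0.5, r = 0.9): 0.1 × 0.3989/0.5 = 0.08 SD
- Rise in the unaffected: 0.02 to 0.32 SD

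A split on the single baseline reading would show apparent improvement in one group and apparent worsening in the other with no effect at all. The split describes the data better but does not isolate therapy.

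**The case against.** The strongest reply is that the study calls itself exploratory, disease outcomes are secondary, and Section 10.3.3 uses associational language. No passage commits the report to a preventive conclusion. The markers are mostly continuous or scored, so they can improve in people below a diagnostic threshold. Training volume is recorded, so change can be related to training done within the arm. The physician health survey runs through every column of the schedule and could pick up new abnormalities.

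Much of this stands as a limit on the point. It does not rescue the purpose as worded. An exploratory label lowers the evidence required but does not supply a comparator. An improved marker in people without the disease is a change in a risk marker, not a prevented case. Participants choose how much they train, so a within-arm relation with volume remains an association. New abnormalities from the survey would have no untrained rate beside them.

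A reader might infer more than the document supports:

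- *That the analysis pools affected and unaffected people and so dilutes any therapeutic effect.* They are enrolled together, but Section 10.2 does not fix one overall test as the only analysis. Baseline status could be a covariate, and the analysis plan, not shown, may separate the groups.
- *That results will be inflated by picking out those abnormal at baseline.* No passage plans that selection. Step 5 of the working is a caution about a possible remedy.
- *That people free of a condition can only get worse.* This is true of a yes/no new-case endpoint, which the protocol does not have.
- *That the course lasts 5 months.* This is inferred from a monitoring column. The post-training assessment is undated, and a figure in Section 4.2 is not shown.

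**Conclusion.** The point holds for the wording of the purpose. With one arm, before/after measurement, no new-onset outcome and at most about 6 months for the last registrants, the study cannot show prevention of age-associated disease. Nor can it attribute a before/after change to training as therapy. This follows from what the protocol fixes and depends on no assumed number.

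The 182 days and the 0.089 SD follow from the document's own dates, target, significance level and power. The case counts, the two-arm sample sizes and the regression-to-the-mean range rest on assumed incidence, prevalence, correlation and risk reduction, none of which the protocol gives. The fault is a claim wider than the design. It is not an error in the primary outcome, and it is not evidence that the planned tests are wrong.

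**What to change.** **Essential.** In Section 1, replace the aim of assessing preventive and therapeutic effects with something like: *to explore the change from the pre-training to the post-training assessment in fitness, risk markers and symptoms of age-associated diseases; no conclusion on disease prevention or on a causal therapeutic effect will be drawn.* Do not write a 5-month duration into this sentence unless the protocol confirms it. Rename Section 10.3.2 so that it no longer announces hypothesis verification, in keeping with the exploratory status in Sections 10.1 and 13.

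**Supporting, in Section 10.3.3.** Report change separately by condition status at baseline. Define status from the drug record (Sections 4.4 and 4.5) where possible, rather than from the single baseline reading. Where the drug record cannot define a condition, say that the baseline reading was used. Show worsening as well as improvement. State that regression to the mean cannot be removed: there is no control, and the single pre-training assessment gives no test-retest correlation to correct with.

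**Cost.** These are wording changes and a grouping of data already planned, with no new visits or measurements. The downside is a narrower claim and smaller groups per condition. Keeping a preventive claim would instead require at least a concurrent control and a new-onset outcome, which is a different study, and at the assumed rates above a far larger one.

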## 2. Subjects

The subjects were middle-aged and elderly persons, aged 40 to 85 years, participating in a health promotion program for middle-aged and elderly citizens, the "Active Health square by The Matsumoto Physical Training Program for Senior Citizens" project.

## 3. Criteria for eligibility

Patients who meet all of the following inclusion criteria, but not any exclusion criteria should be regarded as eligible.

### 3.1. Inclusion criteria

- 1) Persons, aged 40 to 85 years, participating in a health promotion program for middle-aged and elderly citizens, the "Active Health Square by The Matsumoto Physical Training Program for Senior Citizens" project.
- 2) Those who can walk independently.

- 3) Those who have received their home doctors' permission to participate in the study.
- 4) Those who gave us their informed consents after explained about the details of the study.

### 3.2. Exclusion criteria

- 1) Persons who are unable to walk.
- 2) Those who are judged to be inappropriate for participating the study by the lead principal investigator.

### 3.3. Subjects in whom informed consent by a legal representative is necessary and its reasons

No corresponding subject.

## 4. Study methods

### 4.1. Study design

- Single arm intervention

### 4.2. Study outline

The protocol of this study is shown below. Physical characteristics, blood pressure, blood lipids and glucose, peak aerobic capacity ( $VO_{2peak}$ ), thigh muscle strength, CES-D, bone mineral density, and markers for calcium metabolism are measured before and after the IWT regimen.

IWT regimen: Before the start of training, subjects are invited to a community office near their homes and instructed to repeat >5 sets of 3-minute low-intensity walking at ~40% of the pretraining  $VO_{2peak}$  for walking followed by 3-minute high intensity at  $\geq 70\%VO_{2peak}$  for  $\geq 4$  days/wk. The energy expenditure during daily walking at their favorite time and place is monitored with a triaxial accelerometer (Jukudai Mate; Kissei Comtec, Matsumoto, Japan) on the right or left waist on the midclavicular line. A beeping signal alerts participants when a change of intensity is scheduled.

Every 2 weeks, the participants visit a local office to transfer their walking records from the accelerometer to a central server at the administrative center through the Internet for automatic analysis and reporting. Trainers use these reports to track daily walking intensity and other parameters to instruct participants on how best to achieve the target

levels.

[figure not shown]

#### 4.4. Regulations for combined drugs (combination therapy)

Subjects under treatment may take drugs during the intervention period. However, drug administration must be recorded.

#### 4.5. Regulations for dose-reduction and discontinuation

Subjects under treatment may take drugs in parallel. However, drug history must be recorded.

#### 4.6. Management of subjects after the completion of this study

After the completion of this study, the study director will provide advice that may be the most adequate, including the outcome obtained in this study, to subjects.

### 5. Subject assignment

#### 5.1. Subject registration

The study director or coordinators (investigators) should write necessary information in a subject registration sheet, and submit it to a person in charge of registration.

## 5.2. Assignment methods and assignment-regulating factors

This is not applicable because this study is single-arm intervention.

## 6. Outcomes

Primary outcomes: Peak aerobic capacity before and after interval walking training

Secondary outcomes: Age-associated disease symptoms; the symptoms of lifestyle-related diseases (hypertension, hyperglycemia, obesity and dyslipidemia), orthopedic diseases (chronic osteoarthritis and osteoporosis), and psychiatric disorders (insomnia, depression, and dementia)

## 7. Observation/examination items

Measurement schedule

| Period                                         | 1 week
before
pre-training
assessment | Pre-training
assessment | 2 weeks
after the
start of
intervention | Every 2
weeks after
the start of
intervention | 5 months
after the
start of
intervention | Post-training
assessment |
|------------------------------------------------|------------------------------------------------|----------------------------|--------------------------------------------------|--------------------------------------------------------|---------------------------------------------------|-----------------------------|
| Measurement
items                           |                                                |                            |                                                  |                                                        |                                                   |                             |
| Informed consent                               | ○                                              |                            |                                                  |                                                        |                                                   |                             |
| Body Composition
Assessment                 |                                                | ○                          |                                                  |                                                        |                                                   | ○                           |
| Blood pressure                                 |                                                | ○                          |                                                  |                                                        |                                                   | ○                           |
| Physical fitness
test                       |                                                | ○                          |                                                  |                                                        |                                                   | ○                           |
| Blood test                                     |                                                | ○                          |                                                  |                                                        |                                                   | ○                           |
| CES-D                                          |                                                | ○                          |                                                  |                                                        |                                                   | ○                           |
| Bone mineral
density                        |                                                | ○                          |                                                  |                                                        |                                                   | ○                           |
| Markers for
calcium
metabolism           |                                                | ○                          |                                                  |                                                        |                                                   | ○                           |
| Age-associated
disease symptoms             |                                                | ○                          |                                                  |                                                        |                                                   | ○                           |
| Exercise intensity
and volume during
IWT |                                                |                            | ○                                                | ○                                                      | ○                                                 |                             |

|                                                                             |   |   |   |   |   |   |
|-----------------------------------------------------------------------------|---|---|---|---|---|---|
| Transmission of the exercise intensity and volume recorded on a calorimeter |   |   | ○ | ○ | ○ | ○ |
| Health survey by physicians                                                 | △ | △ | △ | △ | △ | △ |
| Adverse events                                                              | △ | △ | △ | △ | △ | △ |

○: Only examination is performed, and the results should be reported if necessary.

△: The development of abnormalities or adverse events must be reported.

●: Reporting is necessary.

## 8. Management of adverse events

### 8.1. Definition of adverse events

#### 8.1.1. Definition of adverse events

Adverse events were defined as all unfavorable or non-intended disorders or signs (including abnormal laboratory data) in study subjects regardless of the presence or absence of a causal relationship with this study.

#### 8.1.2. Definition of severe adverse events

Severe adverse events (SAEs) refer to adverse events corresponding to one of the following items among adverse events:

1. Fatal adverse events
2. Life-threatening adverse events
3. Adverse events requiring admission for treatment or the prolongation of the admission period
4. Those leading to permanent or marked disorders/dysfunction
5. Those that may induce congenital abnormalities in offspring

### 8.2. Management of subjects on the appearance of adverse events

The study director or investigators must inform subjects of the appearance of adverse events, and promptly refer them to adequate medical institutions.

### 8.3. Evaluation of adverse events/reporting

When SAEs occur, the investigators should take necessary measures, such as explanation to subjects, and promptly report them to the study director.

When being informed of the development of an SAE, the study director should promptly prepare “a report on a severe adverse event (1st report)” (Shinshu University School of Medicine clinical research plan Form 4), and report it to the head of the School of Medicine. As a rule, the study director must prepare “a report on a severe adverse event (2nd report)” (Shinshu University School of Medicine clinical research plan Form 5) within 7 days, and report it to the head of the School of Medicine. Furthermore, information on the development of the adverse event should be promptly shared with the investigators involved in this study.

